## Abstract

Child Marriage (CM) is one of the major developmental concerns in Bangladesh, reporting one of the highest rates of CM (59%) globally. To date, interventions to address CM in Bangladesh have failed to seriously engage with social norms that are important contributors to CM. This paper describes the evaluation design of the Tipping Point Initiative that aims to reduce CM through social norm change and increasing adolescent girls’ agency to voice their rights. The Tipping Point Initiative evaluation trial employs a mixed method design. The quantitative component includes a three-arm Cluster Randomized Controlled Trial design, where Arm 1 receives Tipping Point Program (TPP); Arm 2 receives Tipping Point Program Plus (TPP+), a social norms-enhanced version of TPP; and Arm 3 is the Control. The trial covers 51 clusters (villages) in *Pirgacha*, in Rangpur district, randomized into three study arms (17 per arms). From each cluster, a cohort of 25 adolescent girls aged 12–<16 years were selected randomly for participation in the survey and intervention. Further, a cross-section of adults (six males and six females) were randomly selected from each cluster for survey. Qualitative baseline data were collected from two purposively selected intervention villages in each intervention arm. Thirty In-Depth Interviews, eight Key Informant Interviews and 16 Focus Group Discussion were conducted with adolescent girls, boys, adult women and men. Same strategies have been followed at endline. The intervention was implemented from April 2019 to December 2020. The endline was conducted 10 months after the end of intervention. Intention-to-treat analysis approach will be used for impact assessment. Both narrative analysis and Grounded Theory approach will be employed in analysing qualitative data. The learnings are expected to inform programs and policies regarding what works and does not work to address CM in such social norms intervention in Bangladesh.

## Background and rationale

Child Marriage (CM) bears negative impact on the lives and well beings of girls [1]. Globally, around 650 million females are married before they are 18 [2]. The global rate of CM before age 18 is 40% and before age 15 it is 12% [3]. While the risk of CM in South Asia has declined from 50% to 30% within the last decade, this region still contributes to 44% of the global burden of CM [2]. The adverse impact of CM on girls’ physical and mental health has been well documented [4–8]. CM also inhibits developmental opportunities for girls (e.g. education, income earning, etc.) [8–11]. Child brides are at a higher risk of exposure to intimate partner violence [12–14]. Furthermore, children born to child brides are at 60% greater risk of dying in the first year of life [15]. The economic burden of CM is enormous. Thus, a reduction in child marriage by one standard deviation (16.7 percentage points) could increase annual per capita real GDP growth by 0.66 percentage points in emerging and developing countries [16].

The literature has documented several factors that influence CM such as girls’ education, parent’s education [17], religion [18], rural residence [19], household poverty, dowry, gender inequality, safety, and security [20–22]. CM rates tend to be high in the poorest countries and among the poor who are unable to invest in girls for alternative options [23].

Social norms related to CM have been considered as one of the important determinants of CM [24,25]. Social norms that hinder girls’ education and women’s labour force participation; and norms surrounding girls’ sexuality and purity [26] creates a conducive environment for CM [23]. Human behaviours are guided by social norms. People tend to practice what they believe others do in their community and what others will approve of. At the same time, they tend to avoid deviant behaviour considering the sanctions [27,28]. Thus, despite widespread knowledge regarding adverse consequences of CM, its rate continues to be high in many countries due to prevailing social norms [29]. Therefore, in order to address CM effectively it is imperative to understand and change social norms related to CM in any particular community.

### Child marriage in Bangladesh

Bangladesh has the fourth highest prevalence of CM globally [30], and the highest in South Asia, with 59% of the women aged 20–24 reported being married before the age of 18 [31]. Bangladesh also has one of the highest prevalence of very early marriage, that is, girls married by age 15 (19%). There exist large geographical variations in the rate of CM in this country, ranging between 35% and 70%. Poverty, lower level of education, rural residence, pervasive patriarchal social norms, dowry system, concerns about family reputation are cited as important determinants of CM in Bangladesh [19,32]. Even though Bangladesh has undergone a rapid change in its socio-economic and other developmental and health indicators, there has been little shift in the rate of CM, suggesting that social norms play a stronger role than other risk factors.

In recognition of the need to address high rates of CM, both The Child Marriage Restraint Act, 2017 (Act No. 6 of 2017) and the National Action Plan to End Child Marriage (2018–2030) were developed. Both the government and other civil society organizations and NGOs are investing to eliminate CM. Still, CM is pervasive and the rate of reduction in CM is very slow. Over two decades from 1993 to 2017, the median age at first marriage in this country has risen from 14.1 to only 16.0 [31,33]. Decrease in the prevalence of CM in Bangladesh was the slowest among the South Asian countries [34]. Alarming is the fact that according to Bangladesh Demographic and Health Survey from 2014 to 2017 even these slow declines in CM have most recently stalled [31,35].

### Interventions addressing CM

The Sustainable Development Goals, which have a target to end CM by 2030, have accelerated the efforts of the governments, NGOs and research organizations from different parts of the world in tackling CM through different programs and policies In line with that, a variety of interventions have been implemented and tested in different countries including Bangladesh, India, Nepal, Ethiopia, Kenya and Malawi. Common intervention components have included girls’ education, livelihoods/conditional cash transfer, empowerment, and community mobilization [36–41]. There have been evaluations, but not all of them were evaluated rigorously [42–44], which leads to missed opportunities to produce evidence on what works in reducing CM and what does not.

Within Bangladesh, a few promising interventions have been implemented. A Cluster Randomized Controlled Trial on CM showed that financial incentives to delay marriage were successful to reduce the likelihood of CM by 21%. A combination of financial incentive and empowerment or empowerment alone, however, did not show an effect on CM [45]. Another Cluster Randomized Controlled Trial conducted in southern Bangladesh reports that support in education, promotion of livelihood skills, and gender sensitization interventions, each implemented separately, were effective in reducing CM [40].

Although these interventions proved effective, they did not include any social norm change component, an important root cause of CM and thus, they risk not being sustainable. As pointed out by Kalamar [46], Lee-Rife et al. [47], and Cislaghi [25] lack of understanding of social norms and how to change them effectively impede the development of effective and sustainable CM prevention programs.

The Phase 1 of Tipping Point Initiative (TPI) used a participatory and developmental evaluation approach to identify the social norms that perpetuate CM in Bangladesh and Nepal and worked with communities to drive social change [48,49]. Based on the success of phase 1, TPI Phase 2, an integrated social norms intervention was designed by CARE to address child marriage through a focus on building adolescent girls’ agency, creating supporting relations and transforming norms driving CM. This paper presents the study design of the TPI in Bangladesh.

### Tipping point initiative (TPI) in Bangladesh

TPI is designed to address the root causes of CM. The project aspires to address the communities’ social norms that restrict the lives and roles of girls and uphold the practice of CM. TPI’s approach focuses on synchronized engagement with different participant groups to promote the rights of adolescent girls through community-level programming. TPI developed two holistic implementation packages, Tipping Point Program (TPP) and Tipping Point Program Plus (TPP+), following a multi-year phase of formative research, exploration, and community-action research to ensure that the packages were well tailored to address the root causes of CM in these specific communities. The resulting synchronized approaches are rooted in challenging social expectations and repressive norms and promoting girl-driven movement-building and activism; components designed to help adolescent girls to find and collectively step into spaces to engage with and tackle inequality. The TPI implements and tests two 17-months intervention packages that include the following key components. As part of the ‘core’ program package, the TPP includes the following:
Weekly sessions with adolescent girls, adolescent boys, and mothers and fathers of adolescents to separately participate in a curriculum that explores social norms related to gender and CM and adolescent sexual health and rights. Girls Group members also participate in sessions around financial literacy and Village Savings and Loan Associations and leadership empowerment, collective action and civic participation

An enhanced package, TPP+, includes the following components in addition to those outlined above:
Engagement with religious leaders, local government, Union Parishad and community-level influencers through quarterly discussion and dialogues around CM.Quarterly intergroup dialogue sessions that bring core participant groups together in facilitated dialogue and reflection
Identification and training of selected Girl Activist Leaders in campaigning and activism. Once trained, these leaders are linked to other Girls’ Groups and have mentorship to plan and execute their own activities around issues important to them.Activist training for selected boys, fathers, and mothers of adolescent girls to build their capacity as allies and supporters of girls’ activism.Quarterly community-wide social norms activities organized and led by Girls’ Group members around themes, such as mobility, menstruation, dowry, gendered division of labour, family honour, sexual harassment, and girls’ aspirations.

## Methods

### Aims and objectives of the study

The study aims to evaluate the impacts of the TPP and TPP+ models on CM. The specific objectives are to:
Assess the impact of the TPP intervention on reducing child marriage among the adolescent girls participating in TPP.Assess the impact of TPP+ intervention on reducing child marriage among the adolescent girls participating in TPP+.Assess the additional impact of the emphasized social norms change model, TPP+, on child marriage over the impact of the core model, TPP.

### Trial design

The Tipping Point evaluation trial employs a mixed-method design, including quantitative and qualitative components. It includes a three-arm Cluster Randomized Controlled Trial design (Figure 1). The arms are as follows:
Arm 1: Tipping Point Program (TPP), designed to enhance adolescent girls’ personal assets, intrinsic and instrumental agency;Arm 2: Tipping Point Program Plus (TPP+), TPP intervention with additional elements designed to enhance social norms change by engaging community leaders and facilitating girl-led community activities; andArm 3: Pure control

**Figure 1. f0001:**
[figure not shown]
Trial design.

This design will enable us to measure the effect of TPP and TPP+ interventions, as well as the effect of the enhanced social norms component over TPP. The effects will be determined by comparing the three arms as follows:
Arm 1 – Arm 3 = Effect of TPP interventionArm 2 – Arm 3 = Effect of TPP+ interventionArm 2 – Arm 1 = Effect of emphasized social norms change

### Study setting

TP intervention and study covered 51 villages, in purposively selected *Pirgacha upazila* (sub-district) from Rangpur district in Bangladesh. Rangpur was chosen as the prevalence of CM was the highest in this division (85%) and the median age at marriage in this district was the lowest (15 years among women aged 20–49) in the country during project inception [50].

#### Cluster selection and randomization

Villages are considered as clusters or the primary sampling units. Initially, a comprehensive list of villages in *Pirgacha upazila* along with the number of households in each village was prepared following the list obtained from the local statistics office. From the list, 51 villages (17 per arm) were selected through a two-stage approach – identification of clusters and randomization to study arms. First, a village was selected at random from the list of all villages within *Pirgacha upazila*. All villages sharing borders with the first selected village were considered ‘buffer’ villages. We then selected the next village in the north-western direction moving anti-clockwise. In addition to the buffer villages, any village consisting of less than 150 households was excluded to ensure a sufficient number of adolescent girls and boys required to form TP intervention groups. Villages in flood-affected and *char* (i.e. river Islands) areas were also excluded considering difficulties in program implementation in such areas. This procedure was followed until the required number of clusters (51) was achieved. Then, each selected village was randomized into one of the three study arms.

#### Household enumeration

Following cluster selection and randomization a household enumeration exercise was conducted in each of the study villages to collect the socio-demographic information (e.g. sex, age, education, religion, marital status, age at marriage, occupation) needed to form the sampling frame for girl and community surveys. A trained team of data collectors conducted this enumeration using a pre-designed form from 9 January – 18 February 2019. The enumeration team received a 3-day participatory training on the form and field procedures. Enumerators were provided with a household enumeration manual. Special care was taken to provide training on how to collect and check information on age and age at marriage. Enumerators cross checked the date of birth with the birth registration card, if available. Any adult person was eligible to provide information for the enumeration. In most of the cases, the respondent happened to be adult female household members (either the household head or wife of household head).

#### Recruitment of study participants and formation of groups

From the household enumeration data, a list of eligible girls and community members was prepared. Girls were eligible for the study if they were: i) aged 12-<16 years; ii) unmarried; and currently living in the study village. Adult males and females aged 25 or more and currently living in the study village were considered eligible to participate in the community survey.

Simple random samples of 29 eligible girls were drawn from each cluster. We oversampled the girls by 16% to achieve a group size of 25, considering the possibility of refusal. In addition, six eligible adult males and six eligible adult females were selected at random from each village for the community survey. In intervention clusters, the lists of selected girls were provided to the implementing organization, which then approached girls from the list of 29 in random order to invite them to participate in the TPI until they had enrolled the 25 target participants per cluster. These girls were then approached to participate in the study, specifically the baseline survey, by the research team. In control villages, and for the adult community samples in each cluster, the research team directly invited the randomly selected participants to enrol in the study during the baseline survey, administered the consent form and interviewed the individuals.

#### Blinding

No one was blinded to their study arm allocation.

## Trial outcomes

### Primary outcome: child marriage among girls

Child marriage is defined as marriage of a girl before the age of 18 years. CM will be measured among the study participants and the measure will include % of marriage before the age of 18 and 15 years. Comparisons will be made between the intervention and control clusters.

### Secondary outcomes

Secondary outcomes measured are: (1) Intrinsic agency – defined as one’s consciousness of own aspirations, capabilities, and rights [51–53]; (2) Instrumental agency – defined as the action to achieve one’s aspirations and goals [51–53]; (3) Collective agency – defined as the collective action to achieve common goals [51–53]; (4) social norms – defined as the normative expectations and empirical expectations regarding child marriage, and girls’ ability to stand up for their rights [54,55].

The specific secondary outcomes of TP include: (1) Adolescent girl’s self-efficacy in achieving life goals and collective efficacy in preventing CM; (2) Adolescent girl’s aspiration about marriage and education; (3) Adolescent girl’s knowledge about Sexual and Reproductive Health and Rights; (4) Attitudes towards gender and rights among adolescent girls and adult community members; (5) Cohesion among adolescent girl; (6) Communication and negotiation skill of adolescent girls; (7) Adolescent girl’s mobility; (8) Participation in financial activities among adolescent girls; (9) Power relations between adolescent and parents; and (10) Perception of Social norms among adolescent girls and adult community members. The details of the study outcomes are presented in Table 1.

**Table 1. t0001:** Primary and secondary outcomes of the Tipping Point impact evaluation in Bangladesh

SL	Outcomes	Indicator/ domain	Target population	Measurement	Questions/Scale used	Number of items	Cronbach Alpha	KMO	Expected direction of change
**Primary outcomes**									
1.	Child marriage	Rate of CM	Girls	Proportion married before 18 years Proportion married before 15 years	-	-	-	-	
**Secondary outcomes**									
1.	Efficacy	Intrinsic agency – Self-efficacy	Girls	Proportion of girls reported higher self-efficacy (using tertiles of score)	Girls’ perceived confidence in achieving life goals in education, healthcare, mobility, marriage, and income earning	8	0.79	0.80	
		Collective agency – Collective efficacy	Girls	Proportion of girls reported higher collective efficacy (using tertiles of score)	Questions were framed around collective action involving the community around preventing child marriage, preventing violence against girls, etc.	5	0.83	0.79	
2.	Aspirations regarding marriage and education	Intrinsic agency	Girls	Frequencies of aspirations around education and preferred age at marriage	Questions were framed around their desired level of education, age at marriage	-	-	-	
3.	Knowledge regarding Sexual and Reproductive Health and Rights (SRHR)	Intrinsic agency	Girls	Proportion of girls reported correct knowledge on SRHR	Questions were framed around their knowledge about SRHR	-	-	-	
4.	Attitudes regarding gender and rights	Intrinsic agency	Girls	Proportion of girls reported higher gender equitable attitude (using tertiles of score)	Modified version of the Gender-Equitable Men (GEM) Scale [59]. Three sub-scales were constructed for girls	7 items for gender roles	0.70	0.81	
						4 items for attitudes regarding controlling by family members	0.76	0.73	
						8 items for attitudes regarding justification of girls beating	0.78	0.82	
			Adult male and female community members	Proportion of adult community members reported higher gender equitable attitude	Modified version of the Gender-Equitable Men (GEM) Scale [59]. Four sub- scales were constructed for adult community members	4 items for gender roles	0.61	0.70	
						4 items for attitudes regarding controlling by family members	0.94	0.80	
						9 items for attitudes regarding justification of girls beating	0.89	0.91	
						4 items for gender discrimination	0.67	0.71	
5.	Cohesion	Collective agency	Girls	Proportion of girls demonstrated higher cohesion	The neighborhood cohesion scale [60]	13	0.93	0.95	
6.	Communication and negotiation	Instrumental agency -Communication skills	Girls	Proportion of girls demonstrated good communication skills	Communication and negotiation scale developed by Liu et al [61]	10	0.72	0.67	
		Intrinsic agency – Confidence regarding negotiation	Girls	Proportion of girls demonstrated higher confidence regarding negotiation	Three questions were asked to measure confidence in negotiating education, marriage and mobility	3	0.72	0.68	
7.	Mobility	Instrumental agency	Girls	Proportion of girls reported higher mobility	Questions were framed around girl’s ability to move certain places	6	0.53	0.69	
8.	Participation in financial activities	Instrumental agency	Girls	Frequencies of participation in financial activities	Six questions related to their involvement in financial activities were formulated				
9.	Power relation	Connectedness with parents	Girls	Proportion of girls reported high connectedness	Connectedness was measured by asking several questions about their relations with parents	7	0.77	0.82	
		Gender discrimination within family	Girls	Proportion of girls reported low gender discrimination	Questions were asked about their experience of discrimination within family	5	0.58	0.68	
10.	Social norm	Social norms	Girls	Proportion of girls demonstrated positive social norm	around normative expectations regarding girls’ practices	4	0.61	0.69	
			Adult male and female community members	Proportion of adult community members demonstrated positive social norm	Measured using statements about normative expectations (injunctive norms) regarding girls’ practices and parents’ practices	8	0.71	0.80	

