#### Sample size

The sample size for the quantitative component was calculated based on the primary outcome ‘child marriage’ among girls aged between 12 years and below 16. The rate of CM for this age group was unknown. Thus, we assumed a 50% prevalence rate and considered a cluster size of 22 adolescent girls. A life skills intervention in Maharashtra, achieved 19% reduction in CM in the community [38]. Based on this, we assumed a 15% effect size and an Intra-Cluster Correlation of 0.05. Considering 5% significance level and 80% power we required 17 clusters per arm making the total number of clusters 51. Considering a 15% non-response/dropout rate the group size increased to 25 and total sample size increased to 1,275 girls. To assess social norms change we considered child marriage related social norms among the adult community members aged 25 or more as the primary outcome. Since the prevalence of CM related norms is unknown in the study villages, we assumed it to be 50%. Considering a 15% effect size, 5% significance level, 80% power and 5% non-response rate, we required 540 community members from 51 clusters. To ensure participation of both males and females we required six adult males and six adult females from each cluster.

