#### Baseline survey data analysis

The household enumeration data were used to estimate the baseline proportion of child marriage among males (married before age 21) and females (married before age 15, and 18). Using the baseline survey data, the basic background characteristics (e.g. age, education, religion, and ethnic group) of the girl and community samples were compared by arm (control, TPP, and TPP+) to check the arm balance. The arms were considered balanced if there were no or few significant differences in background characteristics.

Descriptive analyses were carried out using the baseline data to report mean score, proportion, tertiles of score for selected outcomes. All group differences were assessed using χ^2^-tests of independence for categorical variables and t-tests for continuous variables. Significance level was set at p < .05 for all bi-variate analyses. The baseline analyses were conducted in STATA 15.

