#### Impact evaluation analysis

Intention-to-treat analysis will be used for assessing the impact of the TP program. Thus, all the TP girls enrolled in TPI will be included in the analysis irrespective of their actual level of participation in the intervention activities. The impact of the TP program on primary outcome, child marriage will be assed using hazard ratio while the TP secondary outcomes will be assessed using risk ratios derived from binary regression analyses for measuring change in outcomes in the intervention arms relative to change in the control arm. Mixed-effects models will be constructed with clusters as random effects and time point, intervention group, and time point x intervention interaction as fixed effects. Adjusting for the dependent variables at baseline survey we will obtain a measure of the relative change in intervention group that took place between baseline and endline compared to the change in the control group. The background characteristics for which the differences between study arms are evident, the pre-existing differences will be controlled in subsequent analyses. All analyses will be adjusted for the potential factors associated with the outcomes of interest.

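### Five girls' scale scores are cut by tertiles and analysed as risk ratios, which loses about a quarter of their information at the protocol's own ICC

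*Protocol article*

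**What the plan says.** Table 1 (Secondary outcomes) gives the measurement of three girls' outcomes in tertile form:

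- Self-efficacy, 8 items: "Proportion of girls reported higher self-efficacy (using tertiles of score".
- Collective efficacy, 5 items: "Proportion of girls reported higher collective efficacy (using tertiles of score".
- Gender attitudes, three sub-scales of 7, 4 and 8 items: "Proportion of girls reported higher gender equitable attitude (using tertiles of score".

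That makes five scores. Most other scale outcomes (cohesion, communication, negotiation, mobility, connectedness, discrimination, norms) are also proportions described as higher, good, high, low or positive, but no cut is named. The adult attitude outcome, for example, is "Proportion of adult community members reported higher gender equitable attitude", with no mention of tertiles.

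Under Impact evaluation analysis, "the TP secondary outcomes will be assessed using risk ratios derived from binary regression analyses". The model has village random effects, a time-by-arm interaction and adjustment for the baseline value of the outcome. Mean scores appear only in the baseline description: "Descriptive analyses were carried out using the baseline data to report mean score, proportion, tertiles of score for selected outcomes".

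**The concern.** The section on scale construction describes factor analysis, item reduction and reliability checks, all aimed at producing graded scores. A risk ratio needs a two-level outcome, so that grading is discarded at the analysis stage. A girl who improves without crossing the cut counts as unchanged, and the effect estimate depends on where the cut falls.

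Agency and attitudes are what the programme sets out to change. The cost is therefore a greater chance of missing a real change in them, which would weaken what the trial can say about how the programme works. The article also does not say whether the tertile boundaries come from baseline or are recomputed at each round, and that affects how the proportions read.

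**Working it through.** **The plan's own figure.** The protocol states no power for the girls' scales. Its only design calculation is for child marriage: "Considering 5% significance level and 80% power we required 17 clusters per arm making the total number of clusters 51". The inputs are 50% prevalence, a 15% effect, ICC 0.05 and 22 girls per village.

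- Reading 15% as percentage points (50% against 35%, two-sided 5%, 80% power) gives 170 girls per arm before clustering.
- The design effect is 1 + 21 × 0.05 = 2.05.
- 170 × 2.05 / 22 = 15.8 villages. Adding the customary one gives 16.8, so 17. With a continuity correction, 183 × 2.05 / 22 = 17.05.

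The 17 villages per arm reproduce. I take the ICC and cluster size from this calculation. Applying that ICC to the scale scores is my assumption.

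**Loss without clustering.** For a normal score cut so that p = 1/3 lie above, the efficiency of the binary outcome relative to the mean is φ(c)² / [p(1−p)]. With c = 0.431 and φ(c) = 0.3636, this is 0.1322 / 0.2222 = 0.595, a loss of 40.5%.

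**Loss with clustering.** Cutting a score also shrinks its ICC. With a latent ICC of 0.05, the bivariate normal calculation gives a binary ICC of 0.0299. With 22 girls per village:

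- Design effect for the score: 1 + 21 × 0.05 = 2.05.
- Design effect for the cut score: 1 + 21 × 0.0299 = 1.63.
- Relative efficiency: 0.595 × 2.05 / 1.63 = 0.75, a loss of about 25%.

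| ICC of the score | Loss, 22 per village | Loss, 25 per village |
|---|---|---|
| 0 | 40.5% | 40.5% |
| 0.02 | 32.4% | 31.5% |
| 0.05 | 25.1% | 23.8% |
| 0.10 | 18.5% | 17.2% |

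**In terms of power.** Each line starts from the effect that a score analysis would detect with 80% power, so the effect differs by ICC. The lines compare methods. They do not show that clustering helps.

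- ICC 0.05, 17 × 22 = 374 girls per arm: d = 2.80 × √(2 × 2.05 / 374) = 0.293. The proportion above the control arm's upper-tertile cut rises from 0.333 to 0.445. The effective size is 374 / 1.63, about 230 per arm. Power is Φ[(0.112 − 1.96 × 0.0455) / 0.0452] = Φ(0.505), about 69%. With 25 per village it is about 70%.
- No clustering: d = 0.205, proportions 0.333 and 0.411, power about 59%.

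**Sensitivity to the normal assumption.** Simulated discrete scores of 5 and 8 items, without clustering, lost 35-40% when roughly symmetric. Skewed scores lost 24-49%, depending on where ties put the cut.

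**Cut-points fixed or recomputed.** Suppose both intervention arms gain 0.3 SD and control gains nothing.

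- Cut fixed at baseline: 33.3% in control against 44.8%, a ratio of 1.34.
- Cut recomputed on the pooled endline sample: 26.3% against 36.9%, a ratio of 1.40. Control girls appear to worsen although nothing changed for them. The contrast between arms is still estimable.

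**The case against.** Proportions and risk ratios are a legitimate summary that programme audiences read easily. Fixing cut-points is often left to an analysis plan, and one may exist that is not shown. Both points are fair. However, the binary risk-ratio analysis is stated for the secondary outcomes and the tertile form for five scores. That is a choice made in the article, not a detail left open.

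Some stronger readings are tempting, and the document does not support them:

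- **That every secondary scale loses this much.** Tertiles are named for five girls' scores only. The other thresholds are unstated and may follow the scale itself. Adults are also sampled at 12 per village, so these girls' figures do not describe them.
- **That the loss is 40%.** That needs an ICC of zero, in a trial whose only stated ICC is 0.05.
- **That change over time cannot show.** The article does not say that tertiles are recomputed. If they were, only the pooled proportion would be held near one third. The planned comparison is change in the intervention arms relative to control, which survives.
- **That all the scales are validated scores being spoiled.** Mobility (alpha 0.53) and family discrimination (0.58) miss the article's own threshold of 0.60.
- **That the test of mediation is damaged.** The article describes no quantitative mediation analysis and assigns pathways of change to the qualitative component.

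**Conclusion.** The point holds for self-efficacy, collective efficacy and the girls' three gender-attitude sub-scales. At the protocol's ICC and cluster size, the cut costs about 25% of the information, and a score analysis with 80% power would drop to about 70%. This rests on a roughly normal score, a shift effect, the top third against the rest, and an ICC for these scores near the value assumed for child marriage. Across ICCs from 0 to 0.10 the loss runs from about 40% down to 17-19%. If the baseline score is also cut when used for adjustment, the loss is larger: about 44-50% at a baseline-endline correlation of 0.3-0.5, ignoring clustering.

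The direction is the same for any scale reduced to two levels, but no figure can be given where no cut is named. Child marriage, its hazard-ratio analysis and the sample size are untouched. This is a worthwhile improvement to the secondary analyses and does not threaten the trial's main conclusion.

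**What to change.** - **Girls' scales.** Make the main analysis of each scale a linear mixed model on the endline score, adjusted for the girl's own baseline score, with a village random intercept. Report mean and standardised differences with confidence intervals.
- **Adult scales.** Adults are separate cross-sections at each round, so they have no individual baseline score. Use the time-by-arm mixed model already stated, on the continuous score.
- **Proportions and risk ratios.** Keep them as supportive results. Set the cut-points once from the pooled baseline distribution, apply them unchanged at endline, and state which group is compared with which.

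The cost is analysis wording, with no new data. The downside is that mean differences are less intuitive for programme audiences, which the retained proportions offset. The change should be recorded before endline comparisons between arms are examined.
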